### SET

The SET program follows the 2019 American Heart Association (AHA) scientific statement on optimal exercise programs for patients with PAD [19]. Each participant completes 36 supervised sessions delivered three times per week over 12 weeks, with each session lasting 60 minutes (45 minutes of structured exercise plus 15 minutes of structured patient education on vascular risk factor management and walking behavior). Treadmill exercise is initiated at 3.2 km/h on a flat gradient; participants walk until claudication pain reaches severity level 3 on a standardized four-point scale, then rest until pain subsides to level 1, repeating for five to six cycles per session.

Structured progression applies as follows: during weeks 1–4, treadmill speed increases by 0.3 km/h every two weeks to a maximum of 4.0 km/h; during weeks 5–8, treadmill grade increases by 1% every two weeks to a maximum of 3%. From week 5, resistance exercises targeting the major lower extremity muscle groups are added, beginning at two sets of 10 repetitions and progressing toward five sets at approximately 70% of one-repetition maximum. Session attendance is documented individually for each participant. Adequate adherence is defined as completion of ≥30 of 36 sessions (≥83%); non-adhering participants are retained in the primary analysis under intention-to-treat principles and analyzed separately in a pre-specified sensitivity analysis. Weekly telephone contact is maintained by a trained exercise physiologist to monitor symptoms and reinforce adherence. Participation in any other formal structured exercise program or rehabilitation intervention during the 12-week SET period is not permitted; habitual daily physical activity and unsupervised walking are allowed.

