3	Alternative composite threshold: ≥100 m absolute MWD gain	Tests sensitivity to an absolute rather than relative distance criterion
4	Functional improvement component only (no revascularization criterion)	Isolates the predictive relationship with functional adaptation. Mandatory pre-specified secondary analysis; reported in all primary publications regardless of composite outcome result.
5	Revascularisation-free survival component only	Isolates the predictive relationship with intervention requirement. Mandatory pre-specified secondary analysis; reported in all primary publications regardless of composite outcome result.
6	Restriction to guideline-concordant revascularisation events only	Removes patient-preference-driven events to reduce confounding; specifically examines discordant cases (functional improvement achieved but revascularisation occurred)
7a	Four-predictor model: muscle density, VAT, age, sex (excluding baseline MWD)	Robustness check with an EPV approximately 10; tests stability of primary model estimates when baseline MWD is excluded
7b	Three-predictor model (muscle density, VAT, age; excluding sex)	Robustness check with an EPV approximately 13–14
8	Alternative muscle density threshold: 33 HU	Tests lower threshold sensitivity for myosteatosis classification (Martin et al. [21] value for BMI ≥ 25 kg/m^2^); see also Section 2.6
9	Alternative muscle density threshold: 41 HU [Martin et al. [21], BMI < 25 kg/m^2^ stratum]	Tests higher threshold sensitivity for myosteatosis classification; see Section 2.6
10	Alternative VAT threshold: --20 cm^2^ (110 cm^2^ M; 80 cm^2^ F)**†**	Tests sensitivity to a more conservative VAT threshold
11	Alternative VAT threshold: +20 cm^2^ (150 cm^2^ M; 120 cm^2^ F)**†**	Tests sensitivity to a more stringent VAT threshold
12	Adherent subgroup (≥30/36 sessions completed)	Per-protocol analysis to assess treatment-specific effects
13	30% treatment failure rate scenario (approximately 30 failures)	Reports model performance and power under a more optimistic clinical assumption
14	Expanded confounding model: primary five predictors plus ABI, smoking status, diabetes, Clinical Frailty Scale score, TASC II classification, SMI, SAT	Pre-specified secondary expanded model; EPV approximately 3–4 (acknowledged limitation); designated as robustness sensitivity analysis; tests whether primary predictor associations are independent of additional clinical confounders

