The composite endpoint comprises four pre-specified outcome combinations, addressed as follows: The primary analysis of treatment failure includes three specific scenarios: (i) program non-completion, defined as failure to attend the requisite number of SET sessions, regardless of functional outcome; (ii) functional non-response among program completers, characterized by completion of the program without achieving the MWD threshold at three months (T1); and (iii) revascularization occurring within the three-month follow-up period, irrespective of functional outcome. This approach aligns with the protocol’s objective of identifying patients capable of deriving sufficient benefit from conservative management alone. The rationale for classifying revascularization as treatment failure, even when accompanied by functional improvement, is that such cases indicate the conservative management pathway was not maintained. Sensitivity analysis #6 (Table 3) examines the subset of guideline-concordant revascularization events separately.

The four pre-specified outcome combinations are: (1) functional improvement achieved AND revascularization-free = treatment success; (2) functional improvement not achieved AND revascularization occurred = treatment failure; (3) functional improvement achieved BUT revascularization occurred = classified as treatment failure in the primary analysis; this discordant case type (functional improvement with revascularization) will be specifically examined in sensitivity analysis #6 (Table 3), restricting to guideline-concordant revascularization events only, to assess whether revascularization was guideline-concordant or driven by patient preference; (4) functional improvement not achieved AND revascularization-free = treatment failure. Failure to meet either criterion (b) or the MWD threshold in (a) constitutes treatment failure.

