### Sample size

Sample size is determined primarily by the precision required for the primary model’s discrimination statistic [26, 27]. A minimum of 40 treatment failures is targeted for the five-predictor primary logistic regression model (muscle density, VAT area, age, sex, baseline MWD), yielding an events per variable (EPV) ratio of approximately 8. This EPV is recognized as modest, providing the primary rationale for the conservative four-predictor robustness check (Table 3, sensitivity analysis #7a). A supplementary power calculation confirms approximately 80% power to detect an odds ratio ≥2.0 per 10 HU decrease in skeletal muscle density (α ═ 0.05, two-tailed).

Assuming a treatment failure rate of 40%, reflecting the program non-completion component of the 40–50% failure rate reported in real-world European SET series [9] and a local institutional audit (approximately 38%); this 40% assumption captures both program non-completion and early revascularization combined, without separately modeling the functional non-response rate among completers. Accounting for 22% attrition from dropout and protocol non-completion, 128 patients must be enrolled to achieve 100 evaluable participants with 40 treatment failures. The IRONIC trial [8], which demonstrated that a significant proportion of claudicants managed conservatively required revascularization during follow-up, supports the clinical relevance of this failure rate, although it was not designed to quantify SET-specific non-response. A pre-specified sensitivity analysis reports model performance under a 30% failure rate scenario (approximately 30 failures, approximately 70% power). All precision-related conclusions are explicitly framed within the derivation cohort boundaries; external validation is necessary before any clinical translation.

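### Sensitivity analysis #12 selects patients on attendance, which is tied to the primary outcome, so it cannot show treatment-specific effects

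*Protocol article*

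**What the plan says.** Row 12 of Table 3 is described as "Adherent subgroup (≥30/36 sessions completed" and its rationale is "Per-protocol analysis to assess treatment-specific effects". The SET section sets adequate adherence at the same 30 of 36 sessions, with three sessions a week for 12 weeks. It adds that "non-adhering participants are retained in the primary analysis under intention-to-treat principles and analyzed separately in a pre-specified sensitivity analysis".

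Primary outcome lists three routes to treatment failure:
- (i) "program non-completion, defined as failure to attend the requisite number of SET sessions, regardless of functional outcome";
- (ii) "functional non-response among program completers";
- (iii) "revascularization occurring within the three-month follow-up period, irrespective of functional outcome".

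Route (i) gives no number of sessions. The 30-session adherence cut-off is the only attendance threshold in the document.

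Sample size plans for 100 evaluable patients with 40 failures. It says the 40% rate covers non-completion and early revascularisation, "without separately modeling the functional non-response rate among completers". Study design and setting states that the study has no comparator.

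**The concern.** Row 12 conditions on session attendance, which is measured after baseline and also decides failure route (i). Selecting on it changes the endpoint as well as the population. H1 and H2 propose that muscle density and VAT area predict failure, and failure includes non-completion, so the predictors may themselves influence who enters row 12.

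The odds ratios in row 12 could differ from the primary ones simply because one kind of failure has gone and the group has been selected. The stated rationale invites readers to take such a difference as something specific to the exercise treatment. A single-arm cohort cannot show that, whichever patients are kept. If the primary binary model is refitted, it would also rest on few events.

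The SET sentence adds an ambiguity. It speaks of analysing non-adherers separately, whereas Table 3 has a row for adherers only.

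**Working it through.** **1. The plan's own figures.** Inputs from Sample size: 100 evaluable, 22% attrition, 40% failure, five predictors.
- Enrolment: 100 / (1 − 0.22) = 128.2, stated as 128. This reproduces.
- Failures: 100 × 0.40 = 40. Events per variable (EPV): 40 / 5 = 8. Both reproduce.

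**2. Failure route (i) against the row 12 rule.**
- Requisite number equal to 30 (or lower): nobody with at least 30 sessions can fail by route (i). All such failures are removed by definition.
- Requisite number above 30, for example 36: a patient with 30–35 sessions is adherent in row 12 but a non-completion failure in the outcome.
- For the non-adherers: if the requisite number is 30 or more, all of them are failures, so no success/failure model can be fitted in that group.

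**3. Failure route (iii) against the row 12 rule.** At three sessions a week, the 30th session falls at 30 / 3 = 10 weeks. A patient whose exercise stops earlier for revascularisation cannot enter row 12. Later events can stay. The document gives no timing of revascularisation. If timing were uniform (an assumption), the share falling before week 10 would be 10/12 = 83% of a 12-week window or 10/13.04 = 77% of a three-month window, leaving 17–23%. Guideline-concordant events require at least 12 weeks of SET (Primary outcome), so they fall at the end of the window and are among those that can stay.

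**4. Events left in row 12.** Sample size attributes all 40 planned failures to non-completion and early revascularisation. If all of these fall outside the adherent group, 100 − 40 = 60 patients remain, and the failures among them are functional non-responders. That rate is not given; 10–30% is assumed.

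| Assumed non-response | Events (60 × rate) | EPV (events / 5) |
|---|---|---|
| 10% | 6 | 1.2 |
| 20% | 12 | 2.4 |
| 30% | 18 | 3.6 |

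If all 128 enrolled patients are analysed, 128 × 0.60 ≈ 77 remain, with 8–23 events and EPV 1.5–4.6. The picture does not change.

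**5. Power, for scale.** Normal approximation: power = Φ(√(n·p·(1 − p)) × ln(OR per SD) − 1.96). For an odds ratio of 2.0 per 10 HU, the stated 80% at n = 100 and p = 0.40 needs a muscle-density SD of about 8.25 HU, which the document does not state:
- Full set: ln 2 × 0.825 = 0.572; √24 × 0.572 − 1.96 = 0.84, giving 80%.
- Row 12, n = 60, p = 0.10: √5.4 × 0.572 − 1.96 = −0.63, giving 26%.
- Row 12, n = 60, p = 0.30: √12.6 × 0.572 − 1.96 = 0.07, giving 53%.

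**The case against.** Restricting to adherers is what per-protocol ordinarily means. Row 12 is one row of Table 3 and cannot alter H1 or H2, whose model is fixed. The document already confines its conclusions to the direction and size of associations. All of that stands, and it limits the severity.

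The event counts rest on an assumed non-response rate and on refitting the binary five-predictor model, which Table 3 does not state for row 12. Leaving functional non-response out of the sample size calculation is also not a forecast that it is zero. This stands too: the counts are a range under stated assumptions.

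The sentence under SET may be a loose reference to row 12, since both use the same cut-off. That is possible. It would then need only rewording.

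Functional response is covered elsewhere: row 4 isolates it, and change in walking distance is a continuous secondary outcome with Spearman correlations. These do not replace row 12. Neither is restricted to completers, and the correlations are not covariate-adjusted.

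A reader might infer that row 12 removes nearly all revascularisation failures, or deletes two of the three failure routes outright. The documents do not support this. They give no revascularisation timing, events after about week 10 can stay, and guideline-concordant events fall late in the window. Route (iii) is reduced, by an unknown amount. Nor can it be said without condition that non-completion failures are all removed, because the requisite number is not defined.

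**Conclusion.** The point holds for the selection rule and the stated purpose of row 12. The analysis selects on a post-baseline variable tied to a component of its own outcome. It is left mainly with functional non-response among completers, plus any late revascularisations, which is a different endpoint from the primary composite. It can describe how the predictors relate to outcome among those who completed, and nothing specific to treatment.

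The undefined session requirement is a fault on either reading. At 30 or below, route (i) disappears from row 12; above 30, row 12 and the outcome disagree about the same patients.

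The size is about 60 patients and 6–18 events (EPV 1.2–3.6, against about 8). This rests on the plan's attribution of its 40 failures, an assumed 10–30% non-response, and a binary five-predictor refit. The severity is modest because the primary hypotheses are untouched.

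**What to change.** 1. Relabel row 12 as *association with functional response conditional on completion (descriptive)* and drop the claim about treatment-specific effects.
2. In patients with at least 30 sessions, regress three-month walking distance, as a continuous outcome, on muscle density, VAT area, age, sex and baseline walking distance. Report how many were revascularised before the three-month assessment and state how they are handled.
3. Under Primary outcome, tie the session requirement of route (i) explicitly to the adherence threshold under SET, or state how the two differ.
4. Align the SET sentence with row 12. Describe non-adherers in a table (sessions attended, walking distance, reasons for stopping), without a success/failure model.

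The cost is one table row and two sentences, using data already planned for collection. Enrolment had not begun when the article was written and no outcome data exist, so the change can be made before any results are seen. The downside is that row 12 leaves the primary odds-ratio scale, and it remains conditional on a post-baseline event, which the new label should make plain.

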### CT body composition analysis

Body composition analysis is derived from a single axial CT slice at the L3 vertebral level. The L3 landmark is defined as the mid-vertebral body of L3, as identified on the scout image, in accordance with the methodology established by Paris et al. (2020) [20]. The L3 landmark serves as a validated systemic whole-body phenotyping tool, though it does not directly measure ischaemia-specific lower limb myopathology. This landmark demonstrates strong correlations with DXA-derived lean and fat mass (r = 0.86–0.94) [13]. Segmentation is conducted using AutoMATiCA [20], a U-Net convolutional neural network validated in multi-morbid clinical cohorts, including critically ill patients, cancer patients, those with liver cirrhosis, and organ donors. However, its performance in PAD-specific imaging, particularly in cases with prevalent vascular calcification, has not been independently verified, a limitation that will be addressed. AutoMATiCA achieves Dice similarity coefficients exceeding 0.97 for skeletal muscle, VAT, and subcutaneous adipose tissue (SAT), while achieving 0.90 for intramuscular adipose tissue (IMAT). The lower accuracy of IMAT segmentation is acknowledged, thus designating it as an exploratory rather than a primary variable in this protocol. The processing time for segmentation is approximately 350 milliseconds per scan.

Routine CTA at our center employs helical (spiral) acquisition. The L3 body composition slice is a reformatted axial image derived from the existing helical dataset, thereby incurring no additional radiation exposure.

Compartment boundaries are determined using a combination of HU thresholds and spatial-mask criteria. Skeletal muscle area is segmented within the muscle fascia boundary using an HU threshold of --29 to +150 HU; structures exceeding 150 HU, such as calcified plaque, are excluded. VAT area is segmented within the peritoneal cavity using an HU range of --150 to --50 HU. SAT area is delineated exterior to the body wall with an HU range of --190 to --30 HU. IMAT area is segmented within the muscle fascia mask, external to individual muscle boundaries, using the same HU range of --190 to --30 HU; SAT and IMAT are differentiated solely by their respective spatial masks. Skeletal muscle density is recorded as the mean attenuation value in HU across the segmented muscle compartment. Detailed parameters, thresholds, and analytical roles are presented in Table 2.

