The primary predictor for H2 is VAT area (cm^2^). Exploratory sex-specific classification thresholds for elevated VAT will be derived separately for men and women by maximizing the Youden index against the binary primary composite outcome, using the same cutpointr bootstrap framework. This threshold derivation is explicitly designated as exploratory and hypothesis-generating, with the continuous z-score employed in the primary model. This approach is preferred over adopting general-population thresholds (>130 cm^2^ in men and >100 cm^2^ in women) from weight-loss and metabolic studies in non-PAD populations [23, 24], as the VAT level at which pro-inflammatory signaling meaningfully constrains exercise adaptation in claudicants has not been established. Sensitivity analyses applying the literature-derived VAT thresholds [23, 24] are pre-specified in Table 3 (sensitivity analyses #10 and #11). The biological rationale for VAT as a cardiometabolic risk marker is discussed in the Introduction [14]. The skeletal muscle index (SMI; cm^2^/m^2^) and SAT area are designated as covariates in the pre-specified secondary expanded model only; they are excluded from the primary model (see Section 2.12). IMAT area is analyzed as an exploratory variable. H3—sarcopenic obesity—is operationally defined as a secondary/descriptive hypothesis by the co-occurrence of skeletal muscle density below the cohort-derived exploratory threshold and VAT area above the cohort-derived sex-specific exploratory threshold, resulting in a four-group phenotype classification: normal (reference group), isolated low muscle density, isolated elevated VAT, and sarcopenic obesity. H3 is not included in the family-wise Bonferroni correction.

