**Continuous predictor modeling**: In the primary model, skeletal muscle density and VAT area are utilized as continuous standardized z-scores. The nonlinearity of each continuous predictor is assessed using restricted cubic splines, with three to five knots selected based on the Akaike Information Criterion. Exploratory cutpoint derivation employing the Youden index (implemented via cutpointr) is conducted as a separate secondary exploratory analysis and is clearly labeled as hypothesis-generating; derived thresholds are not employed in the primary predictive model.

Internal validation is performed using bootstrap resampling (1000 samples), yielding optimism-corrected area under the curve (AUC), calibration slope, and calibration-in-the-large. The bootstrap resampling procedure encompasses the entire analytical pipeline, including nonlinearity assessment (spline knot selection); the same bootstrap samples are utilized for optimism correction across the full pipeline. For any exploratory cutpoint derivation, the derivation step is nested within a distinct independent bootstrap loop to prevent double-counting of optimism. A four-predictor model excluding baseline MWD (skeletal muscle density, VAT area, age, sex; EPV approximately 10) is included as a pre-specified robustness check (Table 3, sensitivity analysis #7a). A three-predictor model excluding sex (EPV approximately 13–14) is also part of the pre-specified robustness checks. For H3, the four-group sarcopenic obesity classification is incorporated as a categorical predictor in a similar model; H3 analyses are reported descriptively and interpreted as exploratory.

**Pre-specified secondary expanded model:** A secondary expanded confounding model is pre-specified, adjusting for the five primary predictors along with additional variables: ABI (continuous), smoking status (categorical), diabetes mellitus (binary), Clinical Frailty Scale score (ordinal), TASC II classification (categorical), SMI (continuous standardized z-score), and SAT area (continuous standardized z-score). This expanded model comprises approximately 12 predictors and, with 40 expected events, yields an EPV of approximately 3–4; this EPV limitation designates the expanded model as a robustness sensitivity analysis rather than a primary inferential tool (Table 3, sensitivity analysis #14). Results will be reported with 95% confidence intervals and interpreted cautiously due to limited EPV.

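### Sensitivity analysis #14 is meant to test independence from clinical confounders but also adjusts for SMI and SAT, so a shrunken H1 or H2 estimate cannot be put down to clinical confounding

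*Protocol article*

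**What the plan says.** Table 3 defines analysis #14 as "Expanded confounding model: primary five predictors plus ABI, smoking status, diabetes, Clinical Frailty Scale score, TASC II classification, SMI, SAT". Its rationale column says that it "tests whether primary predictor associations are independent of additional clinical confounders". The Statistical analysis section, under the pre-specified secondary expanded model, repeats the covariate list and ends it with "SMI (continuous standardized z-score), and SAT area (continuous standardized z-score". It gives the model's size as "This expanded model comprises approximately 12 predictors and, with 40 expected events, yields an EPV of approximately 3–4" and its status as follows: "this EPV limitation designates the expanded model as a robustness sensitivity analysis rather than a primary inferential tool".

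On where the CT variables come from, the CT body composition analysis section states: "Body composition analysis is derived from a single axial CT slice at the L3 vertebral level". It also states: "Skeletal muscle density is recorded as the mean attenuation value in HU across the segmented muscle compartment". Table 2 gives SMI the same HU range (-29 to +150) and the same fascia mask as muscle density. The text on body composition parameters says that SMI and SAT "area are designated as covariates in the pre-specified secondary expanded model only; they are excluded from the primary model".

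**The concern.** The primary model adjusts only for age, sex and baseline MWD. Whether density and VAT predict outcome independently of frailty, diabetes, smoking, ABI and anatomical disease extent is left to #14, and the Limitations text points to the expanded model as the place where TASC II is adjusted for.

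#14 asks two questions in one fit. The first is whether the associations survive adjustment for clinical confounders. The second is whether density and VAT carry information beyond muscle mass and subcutaneous fat. SMI is the height-indexed area of the compartment whose mean attenuation is the H1 predictor. SAT is the neighbouring fat compartment to VAT. A fall in either estimate could answer the first question, the second, or both, and only the first is named in the rationale.

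At stake is the reading of a secondary result. The Discussion confines conclusions to the direction and magnitude of the associations, and magnitude is what these two covariates can move. A reader could take a smaller density or VAT estimate as explained by clinical confounding when the clinical covariates contributed nothing to the change.

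**Working it through.** **1. The plan's own figures.** EPV = events / predictors.
- Expanded model: 5 primary + 5 clinical (ABI, smoking, diabetes, CFS, TASC II) + 2 CT (SMI, SAT) = 12; 40/12 = 3.33. The stated 3–4 reproduces.
- Primary model: 40/5 = 8.0, as stated.

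**2. Does any other listed analysis separate the two blocks?**
- #7a and #7b only remove variables from the primary model.
- #1–6 change the outcome definition; #8–11 change thresholds; #12 restricts to adherent patients; #13 changes the failure-rate scenario; #15 uses complete cases.
- None adds the clinical covariates without SMI and SAT.

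**3. Can the estimate shrink with no clinical confounding at all?** The protocol gives no correlation between density and SMI or between VAT and SAT, so r is an assumption here, ranged from 0 to 0.7. In each large-sample logistic simulation below (N = 400,000, failure about 40%), any clinical covariate fitted is unrelated to density and to outcome.

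*(a) Shared signal.* Density and SMI are both imperfect markers of one underlying muscle trait, and that trait drives outcome (assumed log OR 0.4 per SD). With standardised markers each correlated √r with the trait, the linear approximation gives a density coefficient proportional to √r alone and to √r/(1+r) once SMI is added. The proportional fall is therefore 1 − 1/(1+r) = r/(1+r).

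| r | r/(1+r) | Simulated fall, clinical covariate + SMI | Simulated fall, clinical covariate only |
|---|---|---|---|
| near 0 | 0% | 0.1% | 0% |
| 0.2 | 0.2/1.2 = 16.7% | 16.3% | 0% |
| 0.3 | 0.3/1.3 = 23.1% | 22.8% | 0% |
| 0.5 | 0.5/1.5 = 33.3% | 32.8% | 0% |
| 0.7 | 0.7/1.7 = 41.2% | 40.5% | 0% |

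*(b) SMI has its own effect* (assumed log OR 0.4 per SD for density and for SMI). The density coefficient falls by 14%, 20%, 32% and 40% at r = 0.2, 0.3, 0.5 and 0.7. At r = 0 it does not fall; it rises by 3.5%, through non-collapsibility. The clinical covariate alone again changes it by 0%.

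*(c) SMI has no outcome signal* (density log OR 0.4). The fall is 0%, within 1%, at every r up to 0.7. Only precision suffers: the standard error is multiplied by 1/√(1−r²), which is 1.02, 1.05, 1.15 and 1.40 at r = 0.2, 0.3, 0.5 and 0.7.

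The same algebra applies to VAT with SAT.

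**4. EPV after a split.**
- Clinical-only: 5 + 5 = 10 named predictors; 40/10 = 4.0.
- CT-only: 5 + 2 = 7; 40/7 = 5.7.
- Counted in parameters, assuming three smoking levels (2 parameters), TASC II A–D (3 parameters) and CFS as one linear term, the clinical-only model has 5 + 1 + 2 + 1 + 1 + 3 = 13 and EPV 40/13 = 3.1. The present #14 has 15 and EPV 40/15 = 2.7.

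**The case against.** The strongest reply is that including SMI and SAT is an open and defensible choice. The aim is that density and VAT predict independently, and showing that density matters beyond muscle mass, and visceral beyond subcutaneous fat, is part of that. This stands: the covariates are legitimate, and the fault is that one fit carries both questions under a rationale naming only one.

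Second, in case (b) the fall is removal of omitted-variable bias, since the fit with SMI returns the true coefficient of about 0.40. In case (c) there is no fall at all. Both are correct, so it cannot be said that SMI must distort the estimate. But in (b) what is removed is still not clinical confounding, and case (a) produces the same pattern with no separate SMI effect.

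Third, the protocol already calls #14 a robustness analysis to be read cautiously. That caution rests on EPV alone. Low EPV is a precision problem; the attribution problem would remain in a larger sample.

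Fourth, the Additional measurements section mentions CFS and SPPB as potential confounders in robustness analyses, and an analysis plan not shown could report covariates in blocks. That is possible. However, the article defines no such model, and it fixes both the covariate list and the rationale of #14.

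A reader might go further and infer that #14 cannot be interpreted in either direction. The documents do not support that: if the estimates survive the larger adjustment set, they have passed a stricter test than the one stated.

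**Conclusion.** The point holds for attenuation only. As specified, #14 cannot attribute a shrunken H1 or H2 estimate to clinical confounding, because SMI and SAT enter in the same step and no listed model leaves them out. The possible size is about 16% to 41% of the coefficient at assumed r = 0.2 to 0.7 with shared signal and no clinical confounding. It is negligible if r is near zero or if SMI and SAT carry no outcome signal. The protocol gives none of these correlations, so the range illustrates what could happen and is not a forecast.

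Importance is low to moderate. A reader might infer that the tests of H1 and H2 are compromised; they are not, since SMI and SAT are excluded from the primary model, and alpha and sample size do not depend on #14.

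**What to change.** Split #14 in Table 3 and in the expanded-model paragraph:

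- **14a:** five primary predictors plus ABI, smoking, diabetes, CFS and TASC II. This is the confounding check, and the statement about independence from clinical confounders attaches to it alone.
- **14b:** five primary predictors plus SMI and SAT. This asks whether density and VAT add information beyond the other CT compartments.

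The present combined fit may stay as a further robustness check, described as adjusting for both blocks.

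The cost is one or two extra models and table rows, with no new data. Both models still have low EPV with 40 events, so the cautious reading the protocol already promises should apply to each. Enrolment is planned from June 2026, so the split can be pre-specified before any outcome is seen.
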